## Abstract

**Background:**

Cardiac rehabilitation is very important for the recovery and the secondary prevention of cardiovascular disease, and one of its main strategies is to increase the level of physical activity. Internet and mobile phone based interventions have been successfully used to help people to achieve this. One of the components that are related to the efficacy of these interventions is tailoring of content to the individual. This trial is studying the effect of a longitudinally tailored Internet and mobile phone based intervention that is based on models of health behaviour, on the level of physical activity and the adherence to the intervention, as an extension of a face-to-face cardiac rehabilitation stay.

**Methods/Design:**

A parallel group, cluster randomized controlled trial. The study population is adult participants of a cardiac rehabilitation programme in Norway with home Internet access and mobile phone, who in monthly clusters are randomized to the control or the intervention condition. Participants have access to a website with information regarding cardiac rehabilitation, an online discussion forum and an online activity calendar. Those randomized to the intervention condition, receive in addition tailored content based on models of health behaviour, through the website and mobile text messages. The objective is to assess the effect of the intervention on maintenance of self-management behaviours after the rehabilitation stay. Main outcome is the level of physical activity one month, three months and one year after the end of the cardiac rehabilitation programme. The randomization of clusters is based on a true random number online service, and participants, investigators and outcome assessor are blinded to the condition of the clusters.

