### Aims and hypotheses

Our aim is to assess the effects of a tailored Internet- and mobile-based intervention on maintenance of self-management behaviours after a cardiac rehabilitation stay. Our hypothesis is that the intervention group (tailored) will have higher adherence to the Internet-based intervention, and be more physically active.

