#### Sample size estimation

Power analysis for *a priori* sample size estimation was performed with equivalence test for two-proportions in a cluster-randomized design by the computer program PASS [28]. The participants that attend the cardiac rehabilitation programme together a given month, consist a cluster. Based on previous research with chronic disease self-management [29] it is reasonable to expect that the proportions meeting goals for all self-management behaviours at one-year follow-up will be relatively low *e.g.*, 15% *vs.* 5%. To discover differences of this size between two groups at a 0.05 alpha level and with 0.80 power, we need a total sample of 16 clusters with 15 participants each. We will recruit a total of 17 clusters, equalling continuous recruitment of all the participants of the cardiac rehabilitation programme of Skibotn Centre over 18 months.

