### Procedure

During the first days of the stay of each monthly group at the Centre, a physiotherapist, who is member of the staff there and administrator of the site, presents the website and the study, answers questions and distributes the consent form to the participants that are interested. Then another session is scheduled for those participants that decide to sign the consent form and take part in the study. In this additional session, the participants are registering to the website, fill-in online the baseline questionnaire and they receive training on how to use the website. During these two meetings the potential participants are generally informed of the features of the site and of the two study conditions, but not in such detail that it will be possible for them to understand in which group they belong.

At the end of the rehabilitation stay, participants are offered a repetition Internet-training session, and are being asked to log-on to fill out the Post-rehab questionnaire. The participants are being encouraged to keep visiting the intervention website after they return home, and are given prompts by email and SMS (Short message service) to fill out follow-up questionnaires at 1, 3, and 12 months after leaving the centre.

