### Measures

For an overview of all measures over the different measurement time points, please see Table 1.

**Table 1 T1:** Overview of measures over the different time points of the study

	**Baseline**	**Post-rehab**	**1 month**	**3 months**	**12 months**
Socio-economic status	Y				
Co-morbidity	Y				Y
Alcohol use	Y				Y
Health-related Internet use	Y				Y
Disease related symptoms	Y	Y	Y	Y	Y
iPAQ	Y	Y	Y	Y	Y
Social support	Y	Y	Y	Y	Y
Self-efficacies	Y	Y	Y	Y	Y
HADS	Y	Y	Y	Y	Y
Perceived Tailoring			Y	Y	Y
Stage of change	Y	Y	Y	Y	Y
Decisional balance	Y	Y	Y	Y	Y
Regulatory focus	Y				
7-day smoking abstinence	Y	Y	Y	Y	Y
Quality of life	Y	Y	Y	Y	Y
Usage logging	Y	Y	Y	Y	Y
User evaluation			Y		Y
Return to work	Y		Y	Y	Y

The main outcome for this study is maintenance of physical activity, measured through self-report. Secondary outcomes are self-efficacy, perceived social support and user evaluation of the intervention. In order to link outcomes to use of the intervention we will assess perceived tailoring, and use of the intervention through web logging.

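### The main outcome is set at 1, 3 and 12 months with no lead occasion, while the sample-size reasoning uses one 0.05 alpha and one year only

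*Protocol article*

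**What the plan says.** **Main outcome.** The abstract (Methods/Design) states: "Main outcome is the level of physical activity one month, three months and one year after the end of the cardiac rehabilitation programme". The Measures section says "The main outcome for this study is maintenance of physical activity, measured through self-report" and gives no time point. The Procedure section schedules "follow-up questionnaires at 1, 3, and 12 months after leaving the centre".

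**Analysis.** The Statistical analysis section speaks of primary outcomes in the plural. It plans an ANCOVA of group differences with baseline as covariate, or multilevel mixed regression if clustering is found. It names no occasion as decisive.

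**Sample size.** The Sample size estimation section expects that the "proportions meeting goals for all self-management behaviours at one-year follow-up will be relatively low", with 15% versus 5% as the example. It sets a single alpha of 0.05 and power of 0.80 for that difference, and concludes: "we need a total sample of 16 clusters with 15 participants each". One year is the only time point mentioned there.

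**Aim and hypothesis.** The aim concerns maintenance of self-management behaviours after the stay, and Study strengths presents the one-year follow-up as the means of studying long-term effects. Aims and hypotheses adds: "Our hypothesis is that the intervention group (tailored) will have higher adherence to the Internet-based intervention, and be more physically active". Adherence is not in the outcome list, which reads: "Secondary outcomes are self-efficacy, perceived social support and user evaluation of the intervention". The sentence after that list says that perceived tailoring and logged use are assessed to relate outcomes to use of the intervention.

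**The concern.** The choice of primary endpoint, including its time point, decides what counts as success. It belongs in the protocol. Here the article does define it, but as three occasions of equal standing, whereas the planning section reasons from one occasion and one alpha. The two do not fit together.

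The difference matters for this intervention. The Background says that lifestyle changes are often hard to maintain after rehabilitation. A benefit at one month that has gone by one year is therefore a plausible result. Under the present wording it could be reported as a positive main outcome, although the question of long-term maintenance had been answered in the negative.

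Two related gaps affect interpretation. Adherence is half of the hypothesis but has no place among the outcomes. And the quantity behind the stated power is not the level of physical activity.

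**Working it through.** **1. The plan's own figure.** Inputs from Sample size estimation: 15% versus 5%, alpha 0.05, power 0.80, 16 × 15 = 240 participants, so 120 per arm if split equally. The section does not state sidedness, intraclass correlation (ICC) or equivalence margin, so no unique reproduction is possible. As an approximation I used the usual difference test for two proportions:

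n per arm = [z(α)·√(2·p̄·(1−p̄)) + z(0.80)·√(p1(1−p1) + p2(1−p2))]² / (p1−p2)²

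with p̄ = 0.10, √0.18 = 0.4243, √0.175 = 0.4183 and z(0.80) = 0.842.

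- One-sided: (1.645 × 0.4243 + 0.842 × 0.4183)² / 0.01 ≈ 110.2, so 111 per arm. 111/15 = 7.4, so 8 clusters per arm and 16 in total. Power with 120 per arm is 82.9% at ICC 0 and 80.6% at ICC 0.005.
- Two-sided: (1.960 × 0.4243 + 0.842 × 0.4183)² / 0.01 ≈ 140.1, so 141 per arm. 141/15 = 9.4, so 10 clusters per arm and 20 in total. Power with 120 per arm is about 74% at ICC 0.

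Sixteen clusters is thus recovered only with a one-sided test and an ICC up to about 0.006. The present point does not depend on this. What matters is that the calculation uses one alpha of 0.05 for one comparison at one year.

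**2. The time points side by side.**

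| Section | Quantity | Time point |
|---|---|---|
| Abstract, Methods/Design | Level of physical activity | 1 month, 3 months, 1 year; no ranking |
| Measures | Maintenance of physical activity, self-reported | None given |
| Statistical analysis | Group differences, baseline as covariate | None given |
| Sample size estimation | Proportion meeting goals for all self-management behaviours | One year only |

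**3. What the three occasions could do to the error rate.** The article states no success rule. Assume separate two-sided tests at 0.05, with any one significant result counting as success.

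- Independent tests: 1 − (1 − 0.05)³ = 1 − 0.857375 = 14.3%.
- Correlated tests: simulation of three equally correlated standard normal statistics, 2 million draws, P(any |z| > 1.96).

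| Correlation between occasions | Family-wise error |
|---|---|
| 0 | 14.3% |
| 0.3 | 13.6% |
| 0.5 | 12.5% |
| 0.7 | 10.9% |
| 0.8 | 9.8% |
| 0.9 | 8.4% |

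The article gives no correlation between occasions, hence the range.

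**4. One named occasion against a later correction.** With 12 months named in advance, the error rate is 5% and the alpha in the sample-size paragraph is unchanged. With a Bonferroni split over three occasions, alpha per test is 0.05/3 = 0.0167. Power for 15% versus 5%, with 120 per arm and ICC 0, then falls from 73.6% to 57.6% (two-sided) or from 82.9% to 67.7% (one-sided). These powers refer to the proportion that was sized and are shown only to indicate the cost of a split.

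**5. What was sized.** The sized quantity is a proportion defined over all self-management behaviours. The main outcome is the level of physical activity by questionnaire. A power statement for the first says nothing about the second, at any of the three occasions.

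**The case against.** The strongest reply is that the error inflation is not in the document. Statistical analysis does not say that each occasion is tested separately, and the 0.05 appears only in the sample-size paragraph. No rule says that one positive occasion suffices. Requiring all three would not inflate the error rate, and a single joint test or a summary over time would also fit the idea of maintenance. This stands. A reader might infer that the trial runs at a 10–14% error rate. The documents do not support that as a fact about the plan: the figure is conditional, and it falls to 8.4% if the occasions correlate at 0.9.

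Second, a multiplicity procedure may sit in an analysis plan that is not shown, and a journal article need not reproduce it. This also stands, so its absence is not the point here. What remains is the definition of the main outcome, which the article does give and which disagrees with the time point in its own sample-size reasoning.

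Third, a reader might treat adherence as a further confirmatory claim that raises the error rate again. The text does not support this. No adherence tests at the three follow-ups are planned, the hypothesis joins adherence and activity with an and, and logged use is given a linking role in Measures. What stands is narrower: a hypothesis named in the aims has no rank among the outcomes.

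Fourth, it is tempting to read the ANCOVA sentence as separate models that drop anyone missing at an occasion. The section says neither, and it provides for mixed regression if clustering is found.

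Finally, the one-year sizing does not prove that 12-month physical activity was the intended primary endpoint, since it concerns another quantity. It supports the time point only.

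**Conclusion.** The point holds as a defect in how the main outcome is defined. Three occasions are declared without ranking, while the sample-size reasoning has one alpha and one year and the stated aim is long-term maintenance. The article leaves open which comparison decides the trial.

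The possible size is a family-wise error of about 8–14% in place of 5%. It rests on two assumptions that the article neither states nor excludes: separate two-sided 0.05 tests with any one sufficing, and correlations between occasions from 0 to 0.9. It should be cited only with those conditions attached.

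Two findings need no assumption. Adherence is in the hypothesis but not in the list of main and secondary outcomes. And the stated 0.80 power belongs to the proportion meeting goals for all behaviours, so it does not apply to the level of physical activity.

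**What to change.** - Name IPAQ physical activity at 12 months as the single primary endpoint, and 1 and 3 months as secondary, with the same wording in the abstract, Measures and Statistical analysis.
- State that the primary test is the 12-month contrast between arms, adjusted for baseline and taking account of the monthly cluster.
- List log-based adherence as a secondary outcome, so that the hypothesis and the outcome list agree.
- State in Sample size estimation that the calculation concerns the proportion meeting goals for all self-management behaviours, and that its power does not carry over to the level of physical activity.

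**Cost.** A few sentences and no new data. Trial status says that recruitment is open, so the choice can still be fixed in advance. Early effects could no longer be claimed as the primary result; they would be reported as secondary. The level of physical activity would remain unsized until a separate power calculation is made, for which the article gives no standard deviation or ICC.

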**Discussion:**

The study suggests a theory-based intervention that combines models of health behaviour in an innovative way, in order to tailor the delivered content. The users have been actively involved in its design, and because of the use of Open-Source software, the intervention can easily and at low-cost be reproduced and expanded by others. Challenges are the recruitment in the elderly population and the possible underrepresentation of women in the study sample. Funding by Northern Norway Regional Health Authority.

**Trial registration:**

Trial registry http://www.clinicaltrials.gov: NCT01223170.

## Background

Cardiovascular diseases (CVD) according to the World Health Organization (WHO) are leading causes of death and represent 30% of all global deaths and 48% of the deaths in Europe [1,2]. Moreover, the current trends predict increase in deaths caused by CVD over the next years. Secondary preventive efforts can decrease mortality risk as well as increase health among CVD patients. This study suggests a new approach in supporting the self-management of CVD patients after rehabilitation. The experimental research model that is implied investigates the effectiveness of tailoring an Internet- and mobile-based intervention according to concepts derived from models of health behaviour, and will contribute to develop these further. If successful, concepts from this project can potentially be extended to primary prevention of CVD among high-risk groups.

The prevention policy for CVD is based on strong scientific evidence and is focusing on three major health behaviours: smoking cessation, healthy diet, and increase of physical activity [3-5]. A rehabilitation and secondary preventive strategy based on the adoption of the same health behaviours after the diagnosis and/or symptoms can decrease mortality risk and increase quality of life [4,5]. Involvement in physical activity is a lifestyle modification that is crucial for the post-discharge period. Exercise interventions can cause a 27% reduction in total mortality and a 31% in cardiac mortality in patients with Coronary Heart Disease [6]. Post-discharge physical activity programmes can take place in hospital setting or at home with no significant differences in physiological and psychological outcomes [7]. The achieved lifestyle changes, however, often prove difficult to maintain [8].

Social support might be one way of increasing long-term adherence to exercise. One likely mechanism through which peer support is important in lifestyle change, is by providing modelling of overcoming barriers towards successful behaviour, thus increasing the belief of the individual that he can succeed in changing his own behaviour (self-efficacy) [9]. However, not everyone has the opportunity to participate in face-to-face groups, so the Internet might provide a good alternative *e.g.*[10].

Internet-based interventions have a large potential for reaching people. In 2008, 67% of Norwegians reported having used the Internet for health purposes [11]. In general, reviews of Internet-based interventions might present a rather confusing picture, as the only common ground is the delivery medium. The interventions include online publish of pamphlets, combinations of text-based information and communicative features such as forums, “ask an expert” services, individually computer tailored content, and multimedia iterations. Nevertheless, a review of six Internet-based interventions for supporting diabetes self-management found that five of the six studies reported improvements in health behaviours [12]. A more general review of Interactive Health Communication Applications (IHCA) for people with chronic diseases concluded that these applications improved users’ knowledge, social support, health behaviours and clinical outcomes [13].

Many of the most successful Internet-based interventions for supporting change in health behaviours utilise tailored content. A tailored intervention is an intervention that is adapted to the characteristics of the individual, typically based on responses to a questionnaire [14]. Tailored interventions have generally proven more effective than standardized self-help materials for smoking cessation [15,16]. Previous research has shown that tailored health messages are in general perceived as more interesting and personally relevant, are better liked, read more thoroughly, discussed more, and remembered better compared to non-tailored educational material [17-20].

Although the tailoring component in Internet-based interventions has received some attention, to the best of our knowledge, no studies have yet compared two versions of an Internet-based intervention for supporting CVD self-management with and without tailoring. A system that additionally can monitor physical activity can give feedback to the patient about the efficacy of the exercise, indicating the exercise capacity of the patient [21]. A review of eHealth interventions for increasing physical activity indicated that these could increase the number of steps, walking minutes and level of activity. Physiological indicators validated the indicated increase of physical activity, *i.e.* increase of heart rate and VO_2_ max and decrease of percentage of body fat [22]. From the same review it is suggested that higher utilization and dose of intervention have better results in health behaviour change, that peer support modules increase log-on rates and that most users read the information they received electronically.

In addition to the bibliographic evidence, we conducted a focus group with 11 CVD patients of the Rehabilitation Centre where the study is going to take place. During a semi-structured discussion with them, the potential users of our service expressed the need for continuing support after they are discharged from the rehabilitation centre. They said that, when they go back home, they need help to remain active, to remain in contact with other participants they met at the rehabilitation centre, to set realistic goals, to plan according to those goals and to receive feedback on their effort to remain physically active. One participant suggested: “What if we could get an email every day at a specific time? Time for exercise!” and when the discussion was about the usability of an exercise diary another participant said: “…a diary where you can show others what you have done…maybe it could create some sort of competitive drive between some of the users. It could make it feel more like an obligation”. Generally participants were positive to the idea of a system that could support them in extending the positive impact the rehabilitation programme had on them. To meet that need, we have to find a way to bring the intervention next to the participants in the same way their peers and the personnel is at the Rehabilitation Centre. Mobile technology seems to be the most appropriate tool since it can be portable and be carried by the participant everywhere.

### Aims and hypotheses

Our aim is to assess the effects of a tailored Internet- and mobile-based intervention on maintenance of self-management behaviours after a cardiac rehabilitation stay. Our hypothesis is that the intervention group (tailored) will have higher adherence to the Internet-based intervention, and be more physically active.

## Methods

### Tailoring

Models of health behaviour often form the core of adaptive tailored interventions. It is therefore important to have adequate process measures in these kinds of interventions in order to identify which variables one should tailor to, for whom, and when. Self-efficacy is one of the theoretical constructs thus far having shown the most consistent effects of being tailored to [23]. Studies have indicated that the stage of change for the cardiac rehabilitation patient when entering an exercise programme is related to outcome, and is therefore another relevant variable to tailor interventions to [24]. We propose to combine and extend this research in line with the Health Action Process Approach HAPA [25], through tailoring to different self-efficacies according to where the individual are in their process of change. A third variable that we will tailor on is the individuals’ promotion- or prevention-goal orientation (regulatory focus). Latimer and colleagues have shown that tailoring to regulatory focus can increase both physical activity [26] as well as fruit and vegetable intake [27].

### Study population

#### Participants

The population of the study is recruited among the participants of the Skibotn Rehabilitation Centre’s cardiac rehabilitation programme. Participants to that programme are people with cardiovascular diseases that usually have been discharged from the region’s main hospital, the University Hospital of North Norway, during a period of 6 months before the programme’s start. They are referred to the Centre by their family doctor and a recent cardiac stress test is required. The cost of the four-weeks programme is partially covered by the participants and the Norwegian Health Scheme covers the rest.

